### Data Collection

Data collection will take place for one week in each month of the year for 18 months starting March 2021, resulting in 18 designated weeks of data collection. This will permit evaluation of the variation in morbidity through the fifth and most serious wave of the COVID-19 pandemic in Hong Kong and across seasons, which has been a significant consideration in previous studies. Seasons may be divided into 3-month periods based on historical climatological data with spring as March-May, summer as June-August, autumn as September-November, and winter as December-February. Thus, there will be 3 weeks of data collection in each season. The study will run over 18 months to capture temporal trends as well as seasonal variation of diseases such as influenza. The first full week of each month in which there are no public holidays will be designated as the data collection week to maximize the number of working days. The week will be defined as 7 consecutive days from Sunday-Saturday as most private doctors in Hong Kong work on weekends and public GOPC are open for a half-day on Saturday. Each participating doctor will collect data on consecutive patients during any of the designated weeks of each season for a total of 6 weeks of data collected per doctor. The research team will collect all completed forms after each data collection week. All data will be checked for proper coding and be doubly entered, cleaned, and compiled into a central database for analysis.

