### Data Analysis

The patterns of morbidity in primary care will be presented by descriptive statistics for the prevalence of health problems and diseases, as well as the rates of management activities (referral, investigation, prescription, preventive care), weighted for the proportion of private and public primary care doctors in Hong Kong. The pattern of morbidity will be compared with the previous pattern in 2007-2008. All estimates will be accompanied by 95% CIs.

Stratified estimates in the patterns of morbidity in primary care by public and private doctors will also be reported and compared with the previous pattern in 2007-2008. The influence of the health care sector on morbidity patterns will be assessed by comparing the prevalence and rates of public and private doctors by nonlinear mixed effects analysis with logit link that accounts for potential covariance among health problems from the same doctor.

Factors associated with morbidity and management patterns in primary care will be assessed by nonlinear mixed effects model with logit link to cater for the dichotomous outcomes. Potential factors including patient demographics (age, sex), doctor background characteristics (age, qualifications, years of practice, type of practice, average number of consultations, participation in primary care initiatives), and nature of problem (acute, chronic, preventive) will be taken as covariates in the model. Both univariable and multivariable analyses will be performed. In the multivariable analysis, the presence of multicollinearity will be assessed by examining the tolerance. Factors involved in multicollinearity will only be considered one at a time.

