### Limitations

This study was originally planned and approved prior to the start of the COVID-19 pandemic. We delayed the implementation in the hope that the pandemic would pass quickly but as this has not happened, we will proceed with the expectation that the effect of COVID-19 will be a limitation of the study as it is affecting usual patient health care–seeking behaviors including for chronic disease [34]. We will also seize the opportunity to capture the full period of the worst (fifth) wave of the COVID-19 pandemic in Hong Kong and to examine how stringent pandemic control measures by the Hong Kong Government affect primary care consultations, and presumably the patterns after the surge has eased and things have returned back to normal.

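### Season and pandemic period are missing from the listed covariates and the weighting, although the 18-month window covers spring and summer twice but autumn and winter once

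*Protocol article*

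**What the plan says.** All references are to the protocol article.

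- **Model terms (Data Analysis).** The factor models take "Potential factors including patient demographics (age, sex), doctor background characteristics", which the text itemises, "and nature of problem (acute, chronic, preventive) will be taken as covariates in the model". The sector comparison is a "nonlinear mixed effects analysis with logit link that accounts for potential covariance among health problems from the same doctor". Neither description contains month, season or pandemic phase. The separate Confounding Variables list has four entries (patient demographics, sector, nature of the problem, doctor and practice background) and also omits calendar time.
- **Weighting (Data Analysis).** The prevalence and rate estimates are weighted for the private/public mix of doctors and then compared with 2007-2008. No other weight is named.
- **Calendar (Data Collection).** "Data collection will take place for one week in each month of the year for 18 months starting March 2021", with seasons defined as "spring as March-May, summer as June-August, autumn as September-November, and winter as December-February". The purpose is given as: "The study will run over 18 months to capture temporal trends as well as seasonal variation of diseases such as influenza". Each doctor is to "collect data on consecutive patients during any of the designated weeks of each season", six weeks in total.
- **Why time matters.** Seasonal variation is a secondary outcome. Limitations says that COVID-19 is changing how patients seek care, and adds an intention to "examine how stringent pandemic control measures by the Hong Kong Government affect primary care consultations".

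**The concern.** The article treats calendar time as a driver of what doctors see, and extends collection to 18 months because of it. The lists that say what will be adjusted for then leave it out. Three consequences follow, of unequal strength.

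1. An 18-month window starting in March does not hold the four seasons in equal parts. A pool weighted only by sector gives autumn and winter too little weight, so it can differ from a one-year survey with no change in morbidity. This touches the main aim, the comparison with 2007-2008.
2. If sectors or types of doctor end up with different calendar mixes, a model without a time term attributes part of the seasonal or pandemic difference to sector or to doctor characteristics.
3. Autumn and winter have no second year, so their seasonal estimates carry whatever pandemic phase they fell in.

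**Working it through.** **The plan's own figure.** Sample Size Calculation uses p = 0.5, a 95% interval and a maximum error of 0.005: n = 1.96² × 0.5 × 0.5 / 0.005² = 38,414.6, rounded up to 38,415. This reproduces, so 0.5 points is a fair yardstick for the precision the plan aims at.

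**Season coverage.** With one week per month from March 2021 to August 2022 and the article's season definitions:

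| Season | 2021 | 2021-22 | 2022 | Weeks |
|---|---|---|---|---|
| Spring | 3 | – | 3 | 6 |
| Summer | 3 | – | 3 | 6 |
| Autumn | 3 | – | – | 3 |
| Winter | – | 3 | – | 3 |

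Winter is 3/18 = 16.7% of weeks, against 25% in a full year.

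**Effect on the pooled comparison.** Inputs from the Discussion: upper respiratory infection in 2007-2008 was 26.4% overall, 32.1% in winter (the highest season) and 22.7% in spring (the lowest). Assumptions: equal season weights in 2007-2008, equal numbers of problems per collection week now, and no true change.

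- Summer + autumn = 4 × 26.4 − 32.1 − 22.7 = 50.8. Neither can lie below 22.7, so summer (s) lies between 22.7 and 28.1.
- 18-month pool = (2 × 22.7 + 2s + (50.8 − s) + 32.1) / 6 = (128.3 + s) / 6.

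| Summer | Autumn | Pool | Shift from 26.4 |
|---|---|---|---|
| 22.7 | 28.1 | 25.2 | −1.2 |
| 25.4 | 25.4 | 25.6 | −0.8 |
| 28.1 | 22.7 | 26.1 | −0.3 |

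**Effect on the sector comparison.** The average outside winter is (105.6 − 32.1) / 3 = 24.5, so winter exceeds the rest by 7.6 points. Spurious sector difference = (public winter share − private winter share) × 7.6. The private share is held at 16.7%; the public shares other than 16.7% are assumptions.

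| Public winter share | Spurious difference (points) |
|---|---|
| 16.7% (as scheduled) | 0 |
| 10% | −0.5 |
| 25% | +0.6 |
| 33.3% | +1.3 |

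**Can season and wave be separated?** The article gives no dates for the fifth wave, so I tried four assumed placements. Each model had four seasons plus a wave indicator (five parameters) over the six season-periods.

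- Wave filling exactly the single winter: rank 4 of 5, not estimable.
- Wave in winter and spring 2022, in spring 2022 only, or from winter through summer 2022: rank 5 of 5, estimable if season and wave effects are additive.

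**The case against.** **An article condenses, and the list is not closed.** The covariate sentence is introduced as a set of examples, and the method for a secondary outcome may sit in a fuller plan. This stands in part: a season term is not excluded. But the confounder list has no such opening, and the weighting statement is specific. Followed as written, both leave season out.

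**The design already balances season.** A reader might infer that sector and doctor effects are confounded with calendar time. The article does not support that. Six weeks per doctor, spread over the seasons, reads as one week in each of the six season-periods, which makes the season mix the same in both sectors. Dropout is given as a single overall one-third, with nothing to say that it differs by sector. Uneven participation is possible, because of that dropout, the latitude over which week within a season is used, and a public arm of only 12 doctors. It is not shown. Any resulting bias may also be small: with 12 public and 48 private doctors, 6 weeks and 250 problems a week, the 95% half-width for a sector difference at 26.4% is 1.96 × √[0.264 × 0.736 × (1/18,000 + 1/72,000)] = 0.72 points. With one-third dropout it is 0.88, and clustering by doctor widens it further. Most of the assumed scenarios lie inside that.

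**Inseparability.** A reader might also infer that seasonal variation cannot be told apart from the wave, or that six season-periods are too few for season, trend and wave terms. Neither follows. There are 18 monthly collection weeks, not six time points; spring and summer are each seen twice; and separability turns on wave dates that are not given.

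**Pandemic aim.** Examining control measures appears in Limitations as an opportunity, not among the objectives or outcomes, so no dedicated analysis of it is owed. COVID-19 is already declared a limitation.

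None of this answers the season-mix artefact, which arises even with full, balanced participation.

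**Conclusion.** The point holds in a limited form. The firm part is the comparison with 2007-2008: an 18-month pool weighted only by sector would show upper respiratory infection about 0.3 to 1.2 points too low with no true change, against a 0.5-point error target. This rests on equal season weights in 2007-2008, equal weekly volumes now and use of the whole 18 months as one pool. The range comes from the summer and autumn shares, which the article does not give.

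The sector and doctor-factor part is conditional: zero under the planned schedule, and about 0.5 to 1.3 points in either direction only under assumed imbalances in winter participation.

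The seasonal part is a limit on interpretation. Autumn and winter each rest on one pandemic-year observation, and whether they can be distinguished from the wave is undetermined on what the article states.

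**What to change.** - Add season and a pandemic-phase factor as fixed effects in the sector and factor models, and add both to the confounder list. Fix the dates of the phases before analysis.
- Standardise pooled 18-month estimates to equal season weights before comparing with 2007-2008. The article says that raw data from the earlier survey were available, so the same weights can be applied to both surveys, which removes the equal-weights assumption made above.
- Show that comparison with and without the wave months. If leaving them out removes a whole season, compare the matching seasons only.
- Use spring and summer 2021 versus 2022 as the same-season contrast between periods.
- Label autumn and winter results as single-year and possibly not distinguishable from period effects. If the dated wave proves to fill one of those seasons exactly, say that the two effects are not separately estimable.

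The collection week is known for each record, so this is a change of analysis wording with no new data and no change to the sample size. The price is a few degrees of freedom, slightly wider intervals and a more modest seasonal claim.

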Since the last morbidity study in Hong Kong in 2007-2008 [3], the Hong Kong Government has implemented some primary care initiatives in response to the increasing burden on public general outpatient clinics (GOPC) such as the GOPC Public-Private Partnership, Elderly Health Care Voucher Scheme, and the Vaccination Subsidy Scheme. These aim to encourage patients to seek care in the private sector, particularly for care of chronic diseases. Tracking morbidity and management trends would provide an indication of the impact of these initiatives on the prevalence of chronic disease and its care in both public and private primary care sectors.

Apart from the morbidity pattern, specific information on the management pattern such as prescription, investigation, referral to specialists, health promotion, and disease prevention is important for assuring the quality of primary care services and for identifying support services needed. In 2014-2015, there were an estimated 6 million primary care encounters in the public sector alone [11], which extrapolates to about 30 million primary care encounters in the combined public (20% of total encounters) and private sectors across Hong Kong [12]. The most recent morbidity study found that the Hong Kong referral rate to specialists was 2.5% in 2007-2008 [3], which means that even a small increase of 1% in referral rate would produce a huge relative increase of 40%, translating to an additional 300,000 specialist referrals. Changes in consultation trends in primary care do occur [13], with substantial potential impact on health care service needs and expenditures, and must be monitored.

With an aging population, increasing prevalence of chronic disease, and the implementation of primary care initiatives to shift some of the burden of chronic disease care from the public to the private sector, a primary care morbidity study is timely and important to document and evaluate the impact of these changes.

This study aims to determine the changes in morbidity and management patterns in Hong Kong primary care compared with the patterns identified in the morbidity study conducted in 2007-2008 [3]. Specific objectives include the following:

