#### Encounter Form

Doctors will manually record information on every patient encounter that occurs during the designated data collection week on a standard data collection form. The information on this form includes basic patient demographics (age and sex), whether he/she is a new patient, the presenting problem as stated by the patient, the diagnosis (or corresponding International Classification of Primary Care, Second Edition [ICPC-2] code) as determined by the doctor, the management activities undertaken, drugs prescribed, and preventive care interventions initiated. Doctors can complete most of the form with checkmarks or simple abbreviations and can write in the diagnosis/problem if they are not sure of the ICPC coding. Doctors in the public sector GOPC are already using ICPC coding in their usual practice and may find it routine to record diagnoses in this way. For forms completed with written diagnoses, trained research assistants will translate these to the corresponding ICPC codes.

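### Nature of problem (acute, chronic, preventive) should not be a covariate in multivariable models whose outcome is a diagnosis: it takes the acute/chronic mix out of the doctor and practice coefficients

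*Protocol article*

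**What the plan says.** All references are to the protocol article.

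- Data Analysis, third paragraph, sets out one model family for two kinds of outcome: "Factors associated with morbidity and management patterns in primary care will be assessed by nonlinear mixed effects model with logit link". Its covariates are patient age and sex, a set of doctor and practice characteristics (including practice type and participation in government initiatives), and nature of problem: "nature of problem (acute, chronic, preventive) will be taken as covariates in the model". Nothing limits nature to the management outcomes.
- Confounding Variables lists nature of the health problem as a confounder, with two levels (acute, chronic) and not three.
- Primary Outcomes includes the factors behind the share and distribution of health problems by sector. The fourth objective asks which doctor and practice characteristics go with morbidity and management patterns. The problem or diagnosis is therefore an outcome in these models.
- Encounter Form lists "the diagnosis (or corresponding International Classification of Primary Care, Second Edition [ICPC-2] code) as determined by the doctor" among the recorded items. It names no separate field for acute, chronic or preventive.
- Data Analysis, second paragraph, handles sector separately, by "comparing the prevalence and rates of public and private doctors by nonlinear mixed effects analysis with logit link", with no covariates named.
- For the factor models, "Both univariable and multivariable analyses will be performed". The only model check named is that "the presence of multicollinearity will be assessed by examining the tolerance".

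**The concern.** A confounder is a separate characteristic that influences the outcome and is associated with the factor of interest. Whether a problem is acute or chronic is a property of the problem. If the outcome is whether this problem is hypertension, chronicity is close to part of the answer. Holding it fixed asks only whether one group of doctors sees more hypertension among its chronic problems. It no longer asks whether that group sees more hypertension.

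This touches the study's rationale. The Introduction wants to evaluate initiatives meant to "shift some of the burden of chronic disease care from the public to the private sector". Practice type and participation in such initiatives sit in the same multivariable model as nature of problem. If participating doctors see more chronic disease, the adjusted coefficients for individual chronic diagnoses would tend to hide it.

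There is also a numerical consequence. A diagnosis that is always acute, or always chronic, has no events in the other classes, and a logit model then has no finite estimate for the nature terms.

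**Working it through.** The plan states no figure on this point, so there is none to reproduce. The document gives no acute/chronic mix and no share of any diagnosis by class. All mixes and risks below are assumptions chosen to show the mechanism.

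**Hand calculation.** Take two groups of doctors, A and B. Assume 60% of problems in A and 20% in B are chronic. Assume one diagnosis makes up 30% of chronic problems in both groups and occurs in no other class.

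- Share of all problems: A 0.60 × 0.30 = 0.18; B 0.20 × 0.30 = 0.06.
- Odds ratio without nature: (0.18/0.82)/(0.06/0.94) = 3.44.
- Odds ratio within the chronic class: (0.30/0.70)/(0.30/0.70) = 1.0.

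The 1.0 follows from the equal within-chronic share. If that share is instead 40% in A and 30% in B:

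- Without nature, A has 0.60 × 0.40 = 0.24, so the odds ratio is (0.24/0.76)/(0.06/0.94) = 4.95.
- With nature it is (0.40/0.60)/(0.30/0.70) = 1.56.

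The adjusted figure keeps the within-class difference and loses the difference in mix.

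**Simulation.** Logistic models were fitted to 38,415 problems (the sample size stated in the article), 20% of them in group A, with and without nature. The doctor random effect was omitted because it does not change whether separation occurs. The assumed acute/chronic/preventive mix was B 60/30/10 and A 30/60/10 (strong contrast), or B 50/40/10 and A 40/50/10 (moderate). Diagnosis risk within each class was equal in both groups.

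| Diagnosis (assumed risk by class) | Strong: OR without → with nature | Moderate: OR without → with nature |
|---|---|---|
| Acute only (45% of acute) | 0.42 → 1.04 | 0.77 → 1.07 |
| Chronic only (30% of chronic) | 2.14 → 0.97 | 1.28 → 0.99 |
| All classes (10/20/5%) | 1.32 → 1.03 | 1.13 → 1.04 |

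The group coefficient has a standard error of about 0.04 on the log scale, so the small departures from 1 after adjustment are within sampling error.

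**Estimability.**

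- Acute-only diagnosis, strong contrast: the chronic-level coefficient ran to -11.4, -21.4 and -31.4 at 10, 20 and 30 iterations, and its standard error to 1.7, 248 and 36,861. The group coefficient stayed at 0.04 (standard error 0.04).
- Chronic-only diagnosis with acute as reference: the intercept diverged too. The group coefficient again stayed finite.
- Diagnosis spread over all classes: normal convergence.
- Management outcome (referral, assumed 1.5%, 4% and 2% by class): normal convergence, with standard errors of 0.07 and 0.13 for the nature terms.
- Outcome equal to the chronic class itself: separation is complete and every standard error exceeds 2,500. The article does not name this as a modelled outcome.

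**Would the planned check find it?** Tolerance compares covariates with one another. In the diagnosis models it was 0.87 to 0.99, which raises no alarm. The overlap is between a covariate and the outcome.

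**The case against.** The strongest reply is that the harm is contained. The sector question has stratified estimates with confidence intervals and its own model with no named covariates. Univariable analyses are planned for the other factors, and the descriptive prevalences on which the study is sized do not use the covariate at all. This stands. It rules out an inference a reader might draw, that the public/private comparison as a whole is adjusted away. The text does not put nature into that model; only the Confounding Variables list leaves the possibility open.

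The reply does not rescue the multivariable morbidity models. The univariable results are not adjusted for patient age and sex, and the multivariable results remove the contrast of interest. The useful model, with age, sex, doctor and practice factors but without nature, is not the one specified. Nor is this a detail left out for brevity: the article states the choice.

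Two other stronger readings also fail.

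- A reader might infer that the models cannot be estimated. For single-class diagnoses only the nature terms, and possibly the intercept, lack a finite estimate. Mixed-class diagnoses and the management model tested converge.
- A reader might infer the same circularity for the preventive-care outcome. Encounter Form treats preventive interventions as something the doctor initiates, which can happen at an acute or chronic visit. A preventive problem type may predict that activity without being the same variable, so circularity is not shown.

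Finally, that nature is derived from the diagnosis is an inference from the listed form items; the form itself is not shown. The point does not depend on it, because a separately recorded nature field would still classify the same problem.

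**Conclusion.** The plan is wrong as written, within a limited scope. In multivariable models whose outcome is a diagnosis or problem category, nature of problem is not a confounder. Adjusting for it takes the acute/chronic mix out of the doctor and practice coefficients that the fourth objective and a primary outcome ask for, leaving only within-class contrasts. For single-class diagnoses the nature coefficients have no finite estimate while the others stay finite, and the tolerance check would not reveal this.

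The size depends on mixes the document does not give. In the assumed cases with equal within-class shares, odds ratios from 0.42 to 3.4 all moved to about 1. Where within-class shares differ, part of the difference survives (4.95 becomes 1.56). The sample size and the management models, where nature is a reasonable covariate, are not in question.

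**What to change.** In Data Analysis and Confounding Variables:

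1. State that nature of problem is a covariate only in the management-outcome models.
2. Leave it out of every model whose outcome is a diagnosis or problem category, including the sector model. Keep patient age and sex and the doctor and practice factors there.
3. If chronicity is of interest for morbidity, report it as a stratifier or as an outcome in its own right.
4. Reconcile the two-level definition in Confounding Variables with the three-level one in Data Analysis.

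The cost is a sentence or two of text. The data collected and the sample size do not change.
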